### Participants

2.8

#### Codesign Participants

2.8.1

Codesign workshop participants will include primary care and social care professionals (GPs, practice nurses, practice managers, general practice facilitators, professionals and leaders from social programs within Councils), and older people, aged 60 years and older residing in the participating council areas. Primary care and council professionals will be recruited for workshops through our existing networks of stakeholders with Adelaide PHN, Council partners and general practices within the participating council regions. Primary care and council professionals will be remunerated with $150AUD gift card for participation in the workshop. Port Adelaide Enfield, Walkerville and Prospect councils will assist in recruiting older people from their communities to participate in a workshop. Older people will be remunerated with $50AUD gift card for participation in the workshop. All participants involved in codesign workshops will provide written informed consent.

#### Prescriptions for Connection Participants

2.8.2

Older people who participate in the social prescribing program will be aged 60 years and above, living in the community (not residential care), and willing and able to participate in social activities. Older people will be recruited into the program by referring health professionals. The social prescribing officers will triage referrals and gain permission to be contacted by the researchers for outcome measures and qualitative data collection. All participants will provide written informed consent.

### Data Collection

2.9

A combination of quantitative and qualitative data collection approaches will be used.

#### Quantitative Data

2.9.1

The primary focus is on evaluating the feasibility of implementation of the *Prescriptions for Connection* program, which will be assessed through checklists, recording program referrals and participant engagement, dropouts and withdrawals and checklists of community connection capturing social activities for older people. Social prescribing officers will record numbers of referrals received, referring organisations, reasons for referrals, numbers of older people who consent and participate in the program, and numbers of older people who are ineligible, decline or withdraw participation. Community Connectors will use a checklist to record number of contacts with each older person and types of social activities the older person was connected with.

Secondary outcomes will compare the impact of the social prescribing program on the quality of life, mental wellbeing and loneliness of older people at their commencement of the social prescribing program (baseline), compared to 3 months and 6 months later. Outcome measures will be collected by a member of the research team via Qualtrics surveys either in person or via telephone with the *Prescriptions for Connection* participants., Outcome measures used will be:
1.Quality of life will be measured with two instruments, the quality‐of‐life‐aged care consumers (QOL‐ACC) and the EuroQol five‐dimension health‐related quality of life instrument (EQ‐5D‐5L). The QOL‐ACC is a self‐administered quality of life questionnaire covering six dimensions (mobility, pain management, emotional well‐being, independence, social connection and activities) developed from first principles with older people through extensive qualitative research. The QOL‐ACC has been extensively validated for use in older people [48] including self‐report ability for older people with cognitive impairment [49]. The EQ‐5D‐5L is a widely used quality of life measure which is also able to be applied in economic evaluation. The descriptive system covers five dimensions including mobility, self‐care, usual activities, pain and discomfort and anxiety and depression [50]. The EQ‐5D‐5L also contains a visual analogue scale (VAS), where participants are asked to rate their general health today on a scale between 0 (indicating the worst health you can imagine) and 100 (indicating the best health you can imagine). The EQ‐5D‐5L has been applied extensively in many countries, and population ‘norms’ are available for comparison [51]. The EQ‐5D‐5L is the most widely used preference‐based measure across the health system [51], however the QOL‐ACC performs well in aged care settings [52]. Both the QOL‐ACC and EQ‐5D‐5L will be used for this study to determine how to two measures perform for older people in community settings.2.Mental wellbeing will be measured using the Warwick‐Edinburgh Mental Well‐Being Scale (WEMWBS). The WEMWBS is a validated instrument for measuring mental wellbeing for older adults [53, 54], and previously used in social prescribing research [55]. The WEMWBS consists of 14 positively worded statements of mental health answered using a five‐point Likert scale. The Likert scale represents a score for each item, giving a minimum score of 14 (lower level of mental wellbeing) and maximum score of 70 (higher level of mental wellbeing) [54].3.The UCLA Three‐Item Loneliness Scale is a validated instrument used among community‐dwelling adults, measuring general feelings of loneliness using three items with simplified response categories [56, 57].

Maintenance of the *Prescriptions for Connection* Program will be measured using the Intervention Scalability Assessment Tool (ISAT) [47]. The ISAT contains five domains covering aspects of scale‐up context and proposed implementation requirements, with a summative assessment scoring a readiness for scale‐up assessment [58].

#### Qualitative Data

2.9.2

Implementation determinants will be explored through interviews and focus groups conducted by a member of the research team. Primary care professionals, council staff and volunteers involved in referring and delivering *Prescriptions for Connection* will be invited to participate in qualitative focus groups at a negotiated time convenient to them. All participants in qualitative data collection will provide written informed consent. Three focus groups will be conducted, one with primary care professionals including GPs, practice and community nurses, practice managers and care coordinators, one with local Council staff, and another with Community Connector volunteers, aiming for a total of *n* = 20 participants. Focus groups will explore perspectives of referring, delivering, implementing and sustaining *Prescriptions for Connection*. Interviews will be conducted with a subset of *n* = 20 older people to gain their experiences of the social prescribing program. Interviews will be audio recorded and professionally transcribed for analysis.

#### Data Analysis

2.9.3

Quantitative data will be analysed using SPSS Version 28 statistical software [59]. Checklist numerical data and participant demographics will be analysed descriptively reporting number, frequencies, percentages, mean and SD, median and IQR. Quality of life, mental wellbeing and loneliness scores will be analysed descriptively as utility scores, mean and SD. Utility scores for the QOL‐ACC and EQ‐5D‐5L will be weighted using the Australian value set. To evaluate the difference between time points for quality of life, mental wellbeing and loneliness, pre‐ and postvariables will be analysed using paired *t*‐tests or nonparametric equivalent. Where comparisons are made across more than two time points, corrections to *p*‐values will be made using the Holm‐Bonferroni method. Chi‐squared test for independence will be used to test for any relationship between age group and responses to the outcome measures. *p*‐values of < 0.05 will be considered statistically significant.

Qualitative data from interviews and focus groups will be analysed in Nvivo [60] using thematic codebook analysis according to Braun and Clarke's criteria [61] with findings mapped to the CFIR framework [37] to identify barriers and enablers to implementation.

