**Research Design and Methods:**

This observational feasibility study will use a multiphase mixed methods process and outcomes evaluation. *Prescriptions for Connection*, a social prescribing program, will be co‐designed and implemented in six primary care practices and three council areas. Implementation outcomes will be evaluated using the Reach, Effectiveness, Adoption, Implementation and Maintenance Framework. Qualitative data collection, via focus groups for health and social care providers and interviews for older people, will be based on the Consolidated Framework for Implementation Research to explore barriers and facilitators, and explain outcomes.

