### Phase Three—Implementation

2.6

The implementation of the *Prescriptions for Connection* program will be informed by Phase Two—Codesign outcomes. Through codesign, processes and materials will inform the implementation of *Prescriptions for Connection* as described in Table 2.

**Table 2 hex70506-tbl-0002:** Co‐designed referral pathways, processes and supporting materials for implementing prescriptions for connection.

Program component	Details and implementation
Referral sources	GP, community health services, general practice team members
Participant eligibility	Older people aged 60 years and above living in the community. Experiencing social isolation, loneliness, or seeking more social connection.
Identification methods	Professional judgement or validated screening tool
Referral mechanisms	Phone call, referral form, self‐referral
Volunteer engagement and support	Where is the best place to meet, transport access, goal setting, supporting and training volunteers, number of sessions with volunteer community connector.
Postprogram feedback process	Whether feedback is required to referrer, and if so, what detail of information is provided.

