#### Prescriptions for Connection Program Participants

2.6.1

Community dwelling older people aged 60 years and over will be eligible to participate in the social prescribing program. Further eligibility and exclusion criteria will be determined through codesign workshops. We will aim to recruit up to a maximum of 200 older people for the social prescribing program. Participation in *Prescriptions for Connection* also involves completing the research evaluation of quality of life, mental wellbeing and loneliness outcome measures. Primary care professionals and those involved in delivering the social prescribing program will be invited to participate in qualitative evaluation described below.

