**Setting‐level impact of prescriptions for connection**			
Reach	The proportion and characteristics of older people who participate in the social prescribing program.	– Number of referrals received – Number of older people who consent and participate – Demographics of older people participating in the program – Number of older people who decline or withdraw participation – Number of visits with Community Connector and record of connected social activities for each older person	– Checklist of program referrals and engagement – Checklists of community connection – Demographics form
Effectiveness	The degree to which the social prescription program produced the intended or unintended changes in outcomes.	The following outcomes measured at baseline, 3 months and 6 months: – Quality of life – Mental wellbeing – Loneliness scores	– QOL‐ACC and EQ‐5D‐5L – WEMWBS – UCLA (3 item)

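### Paired tests on three-visit secondary outcomes drop incomplete pairs and ignore site, so the estimated change may be biased and its interval too narrow; a repeated-measures model is a cheap improvement

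*Protocol article*

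**What the plan says.** Table 3 of the Protocol article sets the schedule: "The following outcomes measured at baseline, 3 months and 6 months". Section 2.9.3 (Data Analysis) then fixes the method for change between visits: pre- and "postvariables will be analysed using paired" t-tests or a nonparametric equivalent. The third visit is dealt with only through multiplicity: "Where comparisons are made across more than two time points, corrections to" p-values follow Holm-Bonferroni. Results with p below 0.05 "will be considered statistically significant".

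Section 2.9.1 (Quantitative Data) makes feasibility the primary focus and these outcomes secondary. It foresees loss to follow-up, since the checklists include "recording program referrals and participant engagement, dropouts and withdrawals". No drop-out rate is given.

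The Abstract has the program "implemented in six primary care practices and three council areas". Table 2 lists the referral sources as "GP, community health services, general practice team members" and also allows self-referral. Section 2.6.1 sets a ceiling, not a target: "We will aim to recruit up to a maximum of 200 older people for the social prescribing program".

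**The concern.** A paired test needs both measurements. Anyone who misses one of the two visits leaves that comparison, so the 3-month and 6-month results can rest on different people. If leaving the program is linked to how someone started or how they fared early on, the change in those who remain is not the change in those enrolled. Holm-Bonferroni controls the number of tests and does nothing about this.

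The test also treats participants as independent. They enter through a small number of practices and councils and share officers and volunteers, and section 2.2 wants findings that carry over to other settings. If the amount of change differs between sites, the paired standard error is too small.

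These outcomes are secondary, but they are not idle. The Conclusion (section 4) links the value of the program to feasibility together with significant improvement in quality of life, wellbeing or loneliness, and the findings go to the workshop that rates scale-up (section 2.10). A completer-only gain, or a p-value that is too small, would feed into both.

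**Working it through.** The article states no power, effect size, SD, drop-out rate or ICC, so there is no figure of its own to reproduce. What follows is a sensitivity range.

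**Inputs from the article:** at most 200 participants; six practices; three visits; alpha 0.05 (two-sided assumed); Holm-Bonferroni across visits.

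**Inputs assumed:** correlation 0.6 between visits; drop-out rates and mechanisms; ICC of the change score; equal practice sizes.

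**1. Drop-out related to early change (simulation).** No true change. 10% are lost at random before 3 months; the log-odds of loss after that are -1.4 - s x (3-month change). The paired t-test is baseline against 6 months. Bias is in SDs of the outcome. The Holm column treats the three pairwise contrasts as one family.

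| Enrolled | s | Missing at 6 months | Bias | Rejects, unadjusted | Rejects, Holm |
|---|---|---|---|---|---|
| 200 | 0 | 28% | 0.00 | 5% | 2% |
| 200 | 0.25 | 28% | 0.02 | 6% | 2% |
| 200 | 0.5 | 29% | 0.04 | 8% | 3% |
| 200 | 1.0 | 31% | 0.08 | 19-20% | 9-10% |
| 100 | 1.0 | 31% | 0.08 | 11-12% | 5% |

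In every row the baseline-to-3-month comparison is unbiased, because loss before 3 months was set to be random. A likelihood estimate on all available data has a 6-month bias of about 0.00 SD in every row.

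**2. Drop-out related to baseline.** With loss more likely at low baseline scores (21% and 24% missing), the paired change is off by -0.04 and -0.08 SD, or 0.6 and 1.1 standard errors. An estimate that uses the baselines of those who left is off by about 0.00. The sign is opposite to that in step 1, so the direction of bias depends on the mechanism.

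**3. Direct formula.** Bias = drop-out proportion x (mean change in completers - mean change in drop-outs). At 20% drop-out, with gaps in SDs of change:
- gap 0: 0.20 x 0 = 0
- gap 0.2: 0.20 x 0.2 = 0.04 SD
- gap 0.5: 0.20 x 0.5 = 0.10 SD

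With 160 complete pairs the standard error is 1/sqrt(160) = 0.079 SD, so the last two are 0.5 and 1.3 standard errors.

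**4. Site.** The design effect is DE = 1 + (m - 1) x ICC, where the ICC is that of the change score and m = 200/6 = 33.3. The actual alpha is 2 x (1 - Phi(1.96/sqrt(DE))), before any Holm correction.

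| Change-score ICC | DE | True SE / paired SE | Actual alpha |
|---|---|---|---|
| 0 | 1.00 | 1.00 | 5.0% |
| 0.01 | 1.32 | 1.15 | 8.8% |
| 0.02 | 1.65 | 1.28 | 12.7% |
| 0.05 | 2.62 | 1.62 | 22.6% |

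With 120 participants (20 per practice), an ICC of 0.01 to 0.05 gives 7.2% to 16.0%. In a simulation of 6 x 33 people, practices that differed in level only gave 4.6%, because level cancels in a within-person difference. A change-score ICC of 0.05 gave 22.5%, in line with the formula.

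**The case against.** The strongest reply is that a simple, multiplicity-corrected paired test is adequate for secondary outcomes in a single-arm feasibility study, and that missing-data handling is commonly left to an analysis plan that is not shown. The second half does not dispose of the point, since the article itself names the test. Several other replies do stand and limit it.

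- A reader might infer that the change is biased, and biased towards benefit. The article does not support that. It gives no rate or mechanism and nowhere says that people who do not benefit leave; unrelated drop-out gives no bias, and step 2 shows that the sign can reverse.
- A reader might infer that the intervals are too narrow. That needs change to vary between sites, and the article gives no ICC. Some participants also enter through community health services or self-referral, and two officers work across all three councils (section 2.3), so practice is not clearly the clustering unit and 33 per practice is an upper case.
- The 20% error rate is the worst row, at the recruitment ceiling and before Holm. With Holm it is about 10%.
- A mixed model is no cure-all. When loss depended on the unseen 6-month change, a likelihood estimate kept about 70% of the paired bias in one scenario (0.115 against 0.163 SD).
- The wording on a nonparametric equivalent does not show that the choice will be made after seeing the data, and means are reported either way. No economic evaluation is planned, and nothing says that these estimates will size the later trial.

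**Conclusion.** The point holds in conditional form. The planned test discards incomplete pairs and ignores site, so the change may be biased and its interval may be too narrow.

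Under the assumptions shown, the 6-month bias is 0 to about 0.08 SD, with an unadjusted type I error of about 5% to 20% (about 2% to 10% for that contrast after Holm). Site variation in change would give 5% to 23% for an ICC of 0 to 0.05 at 33 per practice. All of these rest on assumed drop-out, correlation and ICC values, and both ranges include no harm at all. The case for changing the plan is that the alternative costs little if the assumptions prove benign and protects the conclusion about significant improvement if they do not.

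**What to change.** In section 2.9.3, make the main analysis of each secondary outcome one linear mixed model for repeated measures: visit as a fixed effect, unstructured within-person covariance, and all available visits from everyone with a baseline. Report mean change at 3 and 6 months with 95% confidence intervals, and keep the Holm correction. Keep the paired test as a completer sensitivity analysis, and compare the baseline characteristics of completers and drop-outs.

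Examine site (practice or council) as a sensitivity analysis, for example as a fixed effect or with a small-sample correction. With only six practices, and some participants entering by other routes, a random site effect would be poorly estimated as the main analysis.

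Cost: a change of analysis text and slightly more analysis work. No new data are needed, and the planned software (SPSS) fits the model. Intervals may be wider, and the model gives no full protection if drop-out depends on outcomes that were never observed.

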### Phase Five—Maintenance

2.10

A translation workshop will be undertaken with primary care and council stakeholders (*n* = 15). The implementation and evaluation findings of the social prescribing program will be presented to workshop participants, who will be asked to individually evaluate scalability of the social prescribing program using the ISAT [47, 58]. Ratings will be presented to the group, and a discussion will be led to explore sustainability and modifications to the program, and strategies for scale‐up, translation, and testing in larger implementation trials. Workshop outcomes will inform a scalable, sustainable model of social prescribing for older people and associated social prescribing program logic for broader implementation.

## Discussion

3

Social prescribing programs have been found to address loneliness and social isolation, improve health and wellbeing, day‐to‐day functioning, social contacts, health‐related behaviours and healthcare demands [14, 15, 16, 19, 20]. However social prescribing models are in their infancy in Australia. This study is innovative and important to address loneliness and social isolation in older Australians to support healthy ageing [12, 18]. Through tailored design, implementation and evaluation, *Prescriptions for Connection*s is an innovative approach, which has the potential for substantial impact to address the quality of life, wellbeing and loneliness for older people in Adelaide.

Healthy ageing is a priority of government sectors at all levels (Commonwealth, State, Local) in Australia, however, lack of integration between these sectors hinders quality of care to older people [62]. Codesign and collaboration across primary care services, local government Councils, Adelaide PHN and universities ensures robust development of the *Prescriptions for Connection* social prescribing program, that is tailored to suit individuals within the context of their communities. Through codesign, this project builds capacity to implement contextually relevant social prescribing, with opportunities for sustainability and broader scale‐up of the program and evaluation. New evidence gained from this study will explore feasibility and address the impact on nonmedical factors on older people's quality of life, wellbeing and loneliness. Broader adoption of social prescribing has the potential for significant improvements in older Australian's health and quality of life as they age, and to reduce the demand on health systems.

There is value in conducting a feasibility study in the implementation of a social prescribing approach in the Australian setting, given the complexity of multiple sector involvement across primary and local governments. In this study, the use of implementation frameworks (RE‐AIM and CFIR) will provide an in‐depth understanding of factors affecting successful implementation to support a future effectiveness trial. Councils and primary care professionals are the level of government closest to the community and have a key role in promoting thriving communities. A strength of this project is that the concept for trialling social prescription in this target setting originated from the local council. Other innovative examples of tackling health issues in community settings that have been driven by non‐health organisations include social workers in libraries [63].

Additionally, this study design is consistent with recent literature by Dingle, Aggar [26] calling for social prescribing implementation research in Australia and the United Kingdom that uses: (a) multilevel or systems theory frameworks to inform programme design and implementation (RE‐AIM and CFIR); (b) methods developed in collaboration with participants and service providers, involving: COTA representation, primary care providers, councils, researchers, and primary health networks; (c) a core set of outcome measures developed and complemented by framework‐specific measures through literature search, program theory, RE‐AIM and CFIR [4]; factors at multiple levels could be included to ensure a comprehensive understanding of the experience and value of social prescribing (RE‐AIM and CFIR); (d) semistructured interviews will focus on understanding barriers and enablers of engagement in social prescribing in marginalised populations; and (e) focus groups will explore link workers' and community workers' experiences of social prescribing. Thus, the findings from this study evaluating the feasibility of the *Prescriptions for Connection* program will contribute to the international knowledge base for social prescribing.

